### Analysis

#### Sample Size Calculation

The sample size was calculated using the GPower 3.1 program. Considering an alpha risk of 0.05 and power of 0.95, a sample with at least 56 participants is required, randomized into the two groups. We anticipate that 20% of the participants will drop out, so will recruit an additional 12 (6 in each group).

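### The dropout allowance of 12 is 20% of the 56 required, not of the 68 recruited, so a 20% loss leaves about 54 (a minor error: power about 0.94 instead of 0.95)

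*Protocol article*

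**What the plan says.** All the figures stand in one short paragraph of the protocol article, under Sample Size Calculation.

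- Requirement: "Considering an alpha risk of 0.05 and power of 0.95, a sample with at least 56 participants is required, randomized into the two groups".
- Expected loss and allowance: "We anticipate that 20% of the participants will drop out, so will recruit an additional 12 (6 in each group".

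The total to be recruited is not printed. It follows as 56 + 12 = 68, or 34 per arm under the 1:1 allocation described under Participants. Nothing elsewhere in the article restates or corrects these figures.

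**The concern.** The paragraph sets a minimum, names an expected loss, and gives an allowance that is meant to protect the minimum against that loss. The allowance is too small to do so. The loss was taken as a share of the participants needed at the end, whereas people drop out from the number who start. The extra 12 can drop out like anyone else.

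At stake is whether the recruitment target delivers the sample size to which the stated power is attached. A reader who takes the paragraph at face value would believe that 20% dropout is fully covered.

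**Working it through.** **Inputs** (all from Sample Size Calculation): required N = 56 (28 per arm); dropout d = 0.20; allowance 12 (6 per arm); alpha 0.05; power 0.95.

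**1. Reproduce the plan's figure.** Taking the loss as a share of the requirement:

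- 56 x 0.20 = 11.2, rounded up to 12 so that it splits evenly between the arms.
- Equivalently, 56 x 1.20 = 67.2, rounded up to 68.
- Per arm, 28 x 0.20 = 5.6, rounded up to 6.

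This matches the printed allowance exactly, so the N x (1 + d) shortcut was evidently used.

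**2. Apply the stated loss to the number recruited.**

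- 68 x 0.80 = 54.4, so about 54 remain (34 x 0.80 = 27.2, about 27 per arm).
- Shortfall against the minimum: 56 - 54 = 2.

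**3. Loss that 68 can absorb.**

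- (68 - 56)/68 = 12/68 = 17.6%.
- A thirteenth dropout (13/68 = 19.1%) already leaves 55.

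**4. Allowance that matches 20%.**

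- N/(1 - d) = 56/0.80 = 70, that is 28/0.80 = 35 per arm, an allowance of 14.
- Check: 70 x 0.80 = 56.

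**5. Effect on power, given that 56 gives 0.95.** No effect size is needed, because for a fixed effect the test's noncentrality grows with the square root of the number per arm. In the normal approximation, two-sided:

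- At 28 per arm, power 0.95 means a noncentrality of 1.960 + 1.645 = 3.605.
- At 27 per arm it becomes 3.605 x sqrt(27/28) = 3.605 x 0.982 = 3.540.
- Power = Phi(3.540 - 1.960) = Phi(1.580) = 0.943.

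The article states neither sidedness nor the exact test behind the calculation, so the same check was run under several assumptions. Each time the effect was set so that 56 gives 0.95.

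| Assumed test | Power at 54 |
|---|---|
| Two-group z test, two-sided / one-sided | 0.943 / 0.944 |
| Two-group t test, two-sided / one-sided | 0.943 / 0.943 |
| Repeated-measures ANOVA, between groups, 2 or 3 time points (correlation 0.5) | 0.943 |
| Repeated-measures ANOVA, group by time, 2 / 3 time points (correlation 0.5) | 0.943 / 0.942 |

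The result is 0.942 to 0.944 in every case, a loss of 0.6 to 0.8 percentage points.

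**The case against.** The strongest reply is that this changes nothing of substance. Adding a percentage of the requirement is a common shortcut, the gap is two recruits (68 against 70), and power moves by less than one percentage point. No analysis or conclusion depends on it. All of that stands as to weight. It does not remove the discrepancy, because the paragraph sets a floor and its own expected loss takes the trial below it.

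One might also read the 20% as referring to the 56 only. The sentence speaks of the participants, and nothing in the article exempts the additional 12 from dropping out, so this reading does not rescue the figure.

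Two stronger readings are tempting, and the document supports neither.

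- A reader might infer that the trial is materially underpowered. The recomputed power of about 0.94 contradicts that.
- A reader might infer that 56 itself is wrong or unfounded, because the paragraph prints no effect size or test. A journal article commonly leaves these inputs to the full protocol or analysis plan, which are not shown. Guessing them settles nothing: depending on the effect size, the test and the number of measurements assumed, the required total falls on either side of 56. The number cannot be rederived here, which is different from its being wrong.

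**Conclusion.** The point holds as a minor arithmetic error. The allowance of 12 covers about 17.6% dropout, not the stated 20%. At 20%, about 54 participants remain (27 per arm) against a minimum of 56, and power is about 0.94 instead of 0.95.

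The counts rest only on the article's own figures. The power figure rests on the premise that 56 does give 0.95, which cannot be checked from the article, and on dropouts contributing nothing to the analysis, as the allowance itself presumes. The finding does not extend to the choice of 56, to the effect that it was meant to detect, or to the adequacy of the design.

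**What to change.** Revise the last sentence of Sample Size Calculation in one of two ways.

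1. Keep 68 (34 per arm). State that this covers about 17.6% dropout, and that 20% dropout would leave about 54 participants with power of about 0.94. This costs one sentence and no change to recruitment.
2. If the sponsor prefers to cover the full 20%, correct the allowance to 14 (7 per arm), giving 56/0.80 = 70 recruited, 35 per arm. This costs the same sentence and two more participants.

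Printing the total to be recruited, under either option, would let a reader check the allowance at once.

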#### Statistical Analysis

Data analysis will be performed using IBM SPSS software (version 20.0). Descriptive statistics, with mean, standard deviation and percentage. For the inferential analyses, two-way ANOVA with repeated measures will be used and the Bonferroni *post hoc* comparison test will be utilized for a comparative analysis of the results of the control group with the experimental group and within-group changes between pre- and post-intervention periods. The α established as a level of significance will be *p* < 0.05 (95%) for all hypothesis tests performed.

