### Outcome Measures

The evaluations will be carried out before the beginning of the intervention, after 4 weeks of the intervention, and 15 days after the end of the intervention. In the initial assessment, a characterization questionnaire will be applied to obtain socioeconomic and health information.

The primary outcome will be the variable depression (Gorenstein and Andrade, 1996) and the secondary outcomes will be mood (Rohlfs et al., 2008), stress (Luft et al., 2007), sleep quality (Buysse et al., 1989; Bertolazi et al., 2009), quality of life (Power et al., 2005), anxiety (Beck et al., 1988) and physical abilities (Hlatky et al., 1989) of the older adults. The analyzed variables and the respective instruments are listed below in Table 1.

**TABLE 1 T1:** List of variables, instruments used, interpretation and reference.

Variables	Instruments	Interpretation of instruments/cutoff points	Authors (year)/articles
Depressive symptoms	BDI	These ups and downs are considered normal (1–10)/Mild mood disturbance (11–16)/Borderline clinical depression (17–20)/Moderate depression (21–30)/Severe depression (31–40)/Extreme depression (Over 40)	Gorenstein and Andrade (1996)/Validation of a Portuguese version of the BDI and State-Trait anxiety inventory in Brazilian subjects
Sleep quality	PSQI	Good sleep (0–4)/Sleep Disorder (5 or more)	Buysse et al. (1989)/The PSQI: a new instrument for psychiatric practice and research.
	Ese-Br	Scores above 10 suggest the diagnosis of excessive daytime sleepiness	Bertolazi et al. (2009)/Portuguese-language version of the Epworth sleepiness scale: validation for use in Brazil
Quality of life	WHOQOL—OLD	Need to improve (1–2.9)/Regular (3–3.9)/Good (4–4.9)/Very good (5)	Power et al. (2005). Development of the WHOQOL-old module
Stress	PSS	Scores can range from 0 to 56/Not the cut-off point.	Luft et al. (2007). Brazilian version of the Perceived Stress Scale: Translation and validation for the elderly
Mood states	BRUMS	Score can vary from 0 to 16/Not the cut-off point.	Rohlfs et al. (2008). BRUMS: an instrument for early detection of overtraining syndrome.
Anxiety	BAI	Scores between (0–21) indicates very low anxiety/(22–35) indicates moderate anxiety/A grand sum that exceeds 36 is a potential cause for concern.	Beck et al. (1988). An inventory for measuring clinical anxiety: Psychometric properties.

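### Repeated-measures ANOVA with 20% expected dropout becomes, as usually run in SPSS, a complete-case analysis without baseline adjustment; a baseline-adjusted mixed model should replace it

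*Protocol article*

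**What the plan says.** - **Outcome.** Outcome Measures: "The primary outcome will be the variable depression", scored on the Beck Depression Inventory (BDI).
- **Visits.** The same section sets a baseline assessment and two later ones, "after 4 weeks of the intervention, and 15 days after the end of the intervention". The Experimental Group and Control Group sections apply all three to both arms, through online forms.
- **Analysis.** Statistical Analysis: "For the inferential analyses, two-way ANOVA with repeated measures will be used", in SPSS 20.0, for all inferential work. Bonferroni post hoc tests compare the arms and examine "within-group changes between pre- and post-intervention periods".
- **Dropout.** Sample Size Calculation: "a sample with at least 56 participants is required, randomized into the two groups". Then: "We anticipate that 20% of the participants will drop out". The only response is 12 more recruits, six per arm, giving 68.

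The article names no imputation and no model that can use an incomplete participant.

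**The concern.** The usual SPSS repeated-measures ANOVA takes one row per person and drops any row with a missing time point. The named method therefore decides, by default, who is analysed. Extra recruits restore the number of complete cases but not the people who were lost.

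Two things are at stake. First, those who complete every modelled visit are no longer the randomised groups. If people in one arm stop answering for reasons linked to mood, a comparison of depression scores among those left can be biased. Second, data already collected may be discarded, and the baseline score is treated as one more outcome instead of being used as a covariate. Both cost precision in a trial of 68.

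**Working it through.** **1. The plan's own figures.** No effect size, correlation or test is given, so 56 cannot be uniquely reproduced. For a group-by-time test with N participants, m = 3 visits, effect size f and an assumed correlation rho = 0.5, the noncentrality is f²Nm/(1 - rho). N = 56 gives power 0.95 at f = 0.217. The 68 follows as 56 × 1.20 = 67.2, rounded up to 34 per arm. (Dividing 56 by 0.80 would give 70.)

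**2. Complete cases.** With 20% dropout, 68 × 0.80 = 54.4, so about 54 are analysed. If instead 20% missed each later form independently (assumption), 68 × 0.80² = 43.5.

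**3. Power.** With the back-solved f = 0.217 and rho = 0.5, power is 0.950 at 56, 0.942 at 54 and 0.884 at 44. At the planned dropout the loss is trivial.

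**4. Bias with no true effect.** Simulation inputs, all assumed: 34 per arm, between-visit correlation 0.6, about 10% lost by week 4 and 20% by day 15. About 54 participants are then complete, while about 61 have a 4-week score.

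| 4-week contrast | Dropout rises with observed score, exercise arm only | Same mechanism in both arms |
|---|---|---|
| Completers, raw difference | -0.10 to -0.27 SD; type I error 6-16% | about 0; about 5% |
| Completers, change from baseline | about 0 to -0.07 SD; about 5% where bias is near 0 | about 0; about 5% |
| All 4-week data, baseline-adjusted | about 0; 5% | about 0; about 5% |

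The ranges cover weak to strong selection and variants of the mechanism.

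The change contrast is protected for a simple reason. If retention depends on the 4-week score and moves its mean by delta, the baseline mean moves by rho × delta, so change moves by only (1 - rho) × delta. Selection on baseline moves change the other way, and the two partly cancel.

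A separate large-sample check assumed SD 8, rho = 0.5, and dropout driven by the 4-week score in the exercise arm only, with 18-19% lost per arm. The completers' difference in change was -0.46 BDI points, and -0.46/8 = -0.06 SD. This implies delta = -0.46/0.5 = -0.92 points, or about -0.11 SD, for the raw difference.

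**5. Precision at rho = 0.6.** In SD² units and up to a common factor:
- change score: 2(1 - rho) = 0.80
- baseline-adjusted score: 1 - rho² = 0.64
- ratio from adjustment alone: 0.80/0.64 = 1.25
- ratio from deletion: 61/54 = 1.13
- together: 1.25 × 1.13 = 1.41

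The simulated standard errors agree: (0.24/0.206)² = 1.36 and (0.247/0.207)² = 1.42. The excess variance is therefore about 35-40%, and most of it comes from the missing adjustment.

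**6. Dropout on the unseen score.** If loss in the exercise arm depends on the current, unrecorded score, the baseline-adjusted 4-week estimate is biased by -0.073 SD (type I error 6.0%) and completers' change by -0.047 SD (5.3%). Theory gives the same order: (1 - rho²) × delta = 0.64 delta against (1 - rho) × delta = 0.40 delta.

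**Limit.** The comparator simulated was a baseline-adjusted analysis of all 4-week scores, not the full mixed model proposed below.

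**The case against.** **The article is condensed.** It names a model and a package, not a procedure or an analysis set, and an unseen analysis plan could add imputation or use MIXED. This stands as far as it makes deletion conditional. It does not dispose of the point, because repeated-measures ANOVA is a stated choice and its usual form in the named software is complete-case.

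**Only two time points may be modelled.** The post hoc text mentions only pre- and post-intervention. A reader might infer that 4-week scores will certainly be lost through a missed 15-day form; the document does not settle that. With two levels, only those missing the 4-week form drop out, and the gain from the fix is mainly baseline adjustment.

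**Selective dropout is not documented.** A reader might infer that an unsupervised programme will lose its more depressed participants. The intervention section describes remote supervision by professionals and weekly contact, although the Discussion concedes that nobody is present during practice. Both arms receive the same forms, and stopping exercise is not the same as not returning a form. Nothing says that dropout differs by arm or depends on mood.

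**The large bias is not in the main test.** A reader might take the 6-16% type I error as that of the repeated-measures ANOVA. It belongs to the raw 4-week comparison among completers, which is a post hoc contrast here. The group-by-time test compares change, where bias is small. Nor is the 35-40% variance gap mainly a cost of deletion.

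**The alternative is not immune.** It relies on data being missing at random, and step 6 shows it can do slightly worse than change scores when that fails. This stands, and it is why a sensitivity analysis belongs in the fix.

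**Conclusion.** The concern holds in a limited form. As usually run and without imputation, the stated method analyses about 54 of 68 randomised participants and makes no use of baseline as a covariate. The between-arm post hoc comparison at 4 weeks is exposed to a bias of about -0.1 to -0.27 SD, but only if dropout depends on mood in the exercise arm alone. The bias disappears if dropout is random or acts alike in both arms. The group-by-time test is nearly unbiased under dropout on observed scores, at most about -0.07 SD in the variants tried. Its variance is about 35-40% larger than necessary if all three visits are modelled, and about 25% larger from the missing adjustment alone (correlation 0.6 assumed). Power lost to deletion alone is small.

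The documents do not support the stronger conclusion that the primary result is invalid or its error rate broken. This is a should-fix, justified because the remedy is nearly free and has to be settled before data are seen.

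**What to change.** Replace the repeated-measures ANOVA with a linear mixed model for repeated measures, fitted with SPSS MIXED:

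- include all randomised participants with any post-baseline score, in their allocated arm;
- take the 4-week and 15-day scores as outcomes;
- use baseline score, arm, visit and arm-by-visit as fixed effects, with an unstructured within-person covariance;
- make the 4-week between-arm contrast in BDI the primary estimate;
- add one sensitivity analysis for data missing not at random, for example shifting the unobserved exercise-arm scores by a stated range.

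The cost is one or two sentences of analysis text and slightly more analysis work, with the same software and data and no extra participants. The model's missing-at-random assumption should be stated. Participants with no post-baseline score still contribute nothing to it, so the effort to collect forms from those who stop exercising remains important.

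### The repeated-measures ANOVA uses baseline as a level of time, not a covariate, and leaves open which term tests BDI; a baseline-adjusted 4-week comparison would use the same data better

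*Protocol article*

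**What the plan says.** Under Outcome Measures, depression (BDI) is the primary outcome and there are three visits: "The evaluations will be carried out before the beginning of the intervention, after 4 weeks of the intervention", and again 15 days after the programme ends.

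Under Statistical Analysis, "two-way ANOVA with repeated measures will be used" with Bonferroni post hoc tests. The stated purposes are "a comparative analysis of the results of the control group with the experimental group" and change within each group from before to after the intervention. The second purpose makes the pre-intervention visit a level of the time factor. Baseline is not mentioned as a covariate. The section does not say whether the exercise effect is tested by the group main effect, the group-by-time interaction or a between-arm contrast at one visit.

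Under Sample Size Calculation, the inputs given are "alpha risk of 0.05 and power of 0.95", and the result is that "a sample with at least 56 participants is required, randomized into the two groups".

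**The concern.** A two-way repeated-measures ANOVA offers several tests that could each be called the comparison of the arms, and they do not answer the same question.

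- **Group main effect.** It averages the between-arm difference over all visits in the model, including the one before treatment, where randomisation makes the expected difference zero.
- **Group-by-time interaction.** It does not average baseline in. With three visits, however, it is a 2-df test of any departure from parallel profiles and does not itself estimate the 4-week benefit.
- **Raw between-arm contrast at 4 weeks.** It addresses the right visit but ignores each participant's baseline score.

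At stake are the precision of the primary comparison in a trial of 56, and clarity about which number is the result. Type I error of any single one of these tests is not in question.

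**Working it through.** **Inputs from the article.** Alpha 0.05; target power 0.95; 56 participants before dropout, so 28 per arm at 1:1; three visits.

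**Inputs assumed, because the article gives none.** True BDI difference d in SD units (0.5 to 0.92); correlation r between visits (0.3 to 0.8), equal for all pairs; equal variances; two-sided tests; complete data.

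**The plan's own figure.** The 56 cannot be reproduced, since no effect size, correlation or test is stated. Different guesses come to it. A three-visit interaction with r = 0.5 and f = 0.22 gives 56. A two-sided t test with d about 0.98 gives 28 per arm. The figure therefore does not reveal which test was intended.

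**Step 1: what the group main effect estimates.** Write the between-arm differences at the three visits as (0, d, d) if sustained, (0, d, d/2) if halved by follow-up, and (0, d, 0) if gone. Their means are 2/3 d, 1/2 d and 1/3 d.

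**Step 2: noncentrality.** Let N/4 = 14, let δ be the difference at each visit and m the mean of the three.

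- Group main effect: λ = 14·m² / [(1+2r)/3], df 1, 54
- Interaction: λ = 14·Σ(δ − m)² / (1 − r), df 2, 108; Σ = 2d²/3 for a sustained effect
- Raw 4-week contrast: λ = 14·d², df 1, 54
- 4-week BDI adjusted for baseline: λ = 14·d² / (1 − r²), df 1, 53

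With d = 0.5, r = 0.5 and a sustained effect:

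- Group: 14 × 0.1111 / 0.6667 = 2.33, power 0.32
- Interaction: 14 × 0.1667 / 0.5 = 4.67, power 0.46
- Raw 4-week: 14 × 0.25 = 3.50, power 0.45 (0.28 if Bonferroni is applied over three visits)
- Adjusted 4-week: 3.50 / 0.75 = 4.67, power 0.56

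Here the interaction and the adjusted analysis have the same noncentrality. The gap between them comes from spending 2 df instead of 1.

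**Step 3: range, sustained effect (power).**

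| d | r | Group | Interaction | Raw 4-week | Adjusted 4-week |
|---|---|---|---|---|---|
| 0.5 | 0.3 | 0.389 | 0.345 | 0.451 | 0.486 |
| 0.5 | 0.5 | 0.323 | 0.464 | 0.451 | 0.564 |
| 0.5 | 0.7 | 0.278 | 0.692 | 0.451 | 0.730 |
| 0.5 | 0.8 | 0.260 | 0.864 | 0.451 | 0.865 |
| 0.75 | 0.3 | 0.711 | 0.675 | 0.787 | 0.823 |
| 0.75 | 0.5 | 0.614 | 0.824 | 0.787 | 0.889 |
| 0.75 | 0.7 | 0.538 | 0.967 | 0.787 | 0.971 |
| 0.75 | 0.8 | 0.506 | 0.997 | 0.787 | 0.996 |

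The efficiency of the group main effect relative to the adjusted analysis is (4/3)(1 − r²)/(1 + 2r). This is (4/3)(0.75)/2 = 0.50 at r = 0.5 and (4/3)(0.51)/2.4 = 0.28 at r = 0.7.

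**Step 4: effect halved by follow-up, d = 0.5.** The interaction falls to 0.36 (r = 0.5) and 0.56 (r = 0.7), and the group main effect to 0.20 and 0.18. The adjusted 4-week analysis stays at 0.56 and 0.73, because it does not use the follow-up visit.

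**Step 5: a larger d, tied to the stated power.** Suppose the 56 had been sized for the three-visit interaction with a sustained effect at power 0.95. At r = 0.5 that implies d = 0.92, and the adjusted 4-week analysis then has power 0.975. At r = 0.8 it has 0.946. On that supposition the adjusted analysis gains at most about 2.5 points over r = 0.5 to 0.8.

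**The case against.** The strongest reply is that the section never names the group main effect as the test. A reader might infer that the planned ANOVA necessarily averages the pre-treatment visit into the effect and so loses much of its power. The article does not support that. Dilution belongs to one term, not to the model. The reference to change from before to after fits the interaction followed by post hoc contrasts, and neither averages baseline in. This part of the reply stands.

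It is also true that d and r are chosen here and not sourced, and that the loss against the interaction depends on them. With a sustained effect it is under 4 points at r = 0.7 and nil at r = 0.8. The larger gaps need a lower correlation or an effect that fades. That stands too.

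Third, the section mentions only periods before and after the intervention, so time might have two levels. The interaction is then a 1-df test of change and the 2-df complaint falls away. But the group main effect would then be diluted to 1/2 d. The change test has power 0.45 (r = 0.5) and 0.66 (r = 0.7) at d = 0.5, still below 0.56 and 0.73.

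Last, one may say that the decisive term and the covariates belong in a statistical analysis plan. That would answer a complaint of missing detail. It does not answer this one, because the article makes a positive choice of model in which baseline is an outcome level.

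**Conclusion.** The point holds in a limited form. The analysis is valid but does not make the best use of the baseline score, and it leaves open a reading in which the primary effect is diluted by a third or more.

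The size depends on the term used. Against baseline-adjusted BDI at 4 weeks, the group main effect loses heavily: 0.32 against 0.56 at d = 0.5, r = 0.5, sustained. The interaction loses moderately at low to middle correlation (0.46 against 0.56) and practically nothing at r = 0.8. At d = 0.75 the gap to the interaction is 15 points at r = 0.3, 6.5 at r = 0.5 and under 1 at r = 0.7. The raw 4-week contrast has 0.45 at d = 0.5 whatever the correlation.

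In the cases computed, the adjusted 4-week analysis was never worse than any reading of the plan by more than about half a point. All of these figures rest on assumed d, r, equal correlations and complete data. The actual loss cannot be fixed from the article. This is an improvement worth making, not an error that invalidates the trial.

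**What to change.** Under Statistical Analysis, state that the primary analysis is the between-arm difference in BDI at 4 weeks adjusted for baseline BDI, reported with a 95% CI. Either ANCOVA, or a mixed model with the 4-week and follow-up scores as outcomes and baseline BDI as a covariate, would serve. With the mixed model, name the 4-week difference as the primary contrast. Use the same model for the secondary scores. Within-group change can remain as description.

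The cost is small: baseline is already collected, SPSS fits these models, and no participants or visits are added. One follow-on is needed. The sample size statement should be checked against the new primary test and should give the effect size and, where used, the correlation behind the 56. If the 56 was computed for a repeated-measures ANOVA, it would otherwise no longer match the analysis.

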### Participants

The sample will be selected probabilistically with individuals aged 60 years and over from the city of Itajaí (Santa Catarina, Brazil). They will be recruited from a telephone directory of people registered with the Municipal Secretariat for the Promotion of Citizenship. Participants who meet the inclusion criteria will be randomized equally between two groups; the experimental group who will carry out the PE protocol (PEP) and the control group (CG) who will be instructed not to perform any type of PE and to follow their usual daily routines. For group allocation, patients will be randomized with a 1:1 computer-generated allocation^1^ and the researcher responsible for the randomization will not be involved in the evaluations.

To participate in the study, the following inclusion criteria will be respected: individuals of both sexes, aged ≥ 60 years (no maximum age limit); with internet access; able to understand and use the smartphone; with the physical and cognitive ability to understand and perform the exercises safely. The exclusion criteria will consist of elderly people who performed physical activity and/or exercise in the last 3 months, according to the criteria recommended by the World Health Organization (World Health Organization [WHO], 2011) (walks of 150 min per week and/or resistance training with weight for 75–150 min) and elderly people with any condition physical or cognitive that makes it impossible to practice the proposed exercises at home.

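### The primary depression outcome has no designated deciding test or visit, and within-arm pre-post changes are listed among the tests at 0.05

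*Protocol article*

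**What the plan says.** Under Outcome Measures, "The primary outcome will be the variable depression", measured by the BDI (Table 1). Assessments are at baseline, "after 4 weeks of the intervention, and 15 days after the end of the intervention". No visit is marked as primary.

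Under Participants, "patients will be randomized with a 1:1 computer-generated allocation", which gives two equal arms.

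Under Statistical Analysis, "two-way ANOVA with repeated measures will be used" for inference, with Bonferroni post hoc comparisons for a "comparative analysis of the results of the control group with the experimental group and within-group changes between pre- and post-intervention periods". The 0.05 level is set "for all hypothesis tests performed". None of the three F tests (group, time, group by time), no post hoc contrast and no visit is named as the one that answers the primary question. The family over which Bonferroni runs is not defined.

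Under Sample Size Calculation, "Considering an alpha risk of 0.05 and power of 0.95", and "a sample with at least 56 participants is required, randomized into the two groups". This too is tied to no contrast.

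**The concern.** The trial is randomised so that exercise can be compared with control. A pre-post test inside one arm does not use the randomisation: it asks whether scores moved, not whether exercise moved them. If mood drifts in both arms for any common reason, the exercise arm can show a significant change with no exercise effect. By chance the control arm may just miss significance in the same trial. A plan that places such tests among its inferential analyses, and names no deciding between-arm test, leaves open a headline conclusion that is not a randomised comparison.

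The second issue is choice. With one primary variable, two post-baseline visits and three F tests, several results could be called the primary one after the data are seen. The third is efficiency: baseline BDI is collected from everyone, but no stated comparison adjusts for it.

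**Working it through.** **Does the sample size reveal the primary contrast?** No. The stated 56 cannot be derived from alpha 0.05 and power 0.95 alone, because effect size, test and correlation are not given. One assumed route comes close: an interaction test with f = 0.25, two visits and r = 0.5 has noncentrality f² × N × m / (1 − r) = 0.0625 × 56 × 2 / 0.5 = 14 and power 0.957, and the smallest N is 54. With the three visits actually planned, the same route gives 44. So 56 does not identify a contrast.

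**Inputs.** From the protocol article: two arms, 1:1, three visits, 28 per arm (56/2). After loss, 68 × 0.8 = 54.4, or about 27 per arm. Assumed, because the article does not give them: SD 1 at each visit, equal correlation r = 0.5 or 0.7 between visits, a shared improvement s of 0, 0.3 or 0.5 SD, and Bonferroni over the three visit pairs (0.05/3 = 0.0167, two-sided).

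**1. Within-arm tests when exercise does nothing.** The paired test has noncentrality s√n / √(2(1 − r)). Call its rejection probability p. The arms are independent, so a significant exercise arm with a non-significant control arm has probability p(1 − p). With n = 27:

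| r | s | noncentrality | p, exercise arm significant | p(1 − p) |
|---|---|---|---|---|
| 0.5 | 0.3 | 1.56 | 0.18 | 0.15 |
| 0.5 | 0.5 | 2.60 | 0.52 | 0.25 |
| 0.7 | 0.3 | 2.01 | 0.31 | 0.21 |
| 0.7 | 0.5 | 3.35 | 0.78 | 0.17 |

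With s = 0, the two-sided rate is 0.0167 and half of it, 0.0083, lies in the direction of improvement. The false pattern in that direction is 0.0083 × (1 − 0.0167) = 0.008, about 1% (1.6% counting either direction). Simulation with 28 per arm agrees: 0.15 to 0.24 with a shared improvement and 0.017 in either direction without one.

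**2. Between-arm tests at two visits.** If there is no arm difference and each post-baseline visit is tested at 0.05, the chance of at least one rejection is 0.091 (r = 0.5) or 0.083 (r = 0.7), so 8-9%. At 0.025 per visit it is 0.046 or 0.043, so 4-5%. In simulation the interaction F test alone stays at 0.048 to 0.052.

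**3. Power for a 4-week effect.** Assume d = 0.8 SD, r = 0.5, 28 per arm, two-sided 0.05.

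- Unadjusted comparison: d√(n/2) = 0.8 × √14 = 2.99, power 0.84.
- Baseline-adjusted comparison: 2.99 / √(1 − r²) = 2.99 / 0.866 = 3.46, power 0.92.
- Interaction on 2 df: noncentrality (n/2) × Σ(d_t − mean)² / (1 − r), where d_t is the arm difference at each visit. If the effect persists fully to 15 days, or vanishes by then, this is 14 × 0.427 / 0.5 = 11.9 and power is 0.87. If half persists, it is 14 × 0.32 / 0.5 = 8.96 and power is 0.76. Simulation gave 0.76 to 0.88.

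In simulation the baseline-adjusted 4-week test kept its error at 0.049 to 0.052 in every null scenario, including those in which both arms improved.

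**The case against.** The strongest reply is that the plan already contains a sound test. The group-by-time interaction compares the arms and holds its error near 0.05. Post hoc tests are by convention subordinate to the model, and the sentence puts the comparison of arms before the within-group changes. All of that stands. A reader might infer that the ANOVA is invalid, that all the tests have equal standing, or that the sponsor will claim efficacy from a change in one arm. The text says none of these things. It only leaves them open, because nothing is named as decisive.

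The size of the within-arm error also depends on a premise that the article does not supply. It gives no figure for a shared improvement, and without one the false pattern is about 1%. Regression to the mean is a weak argument here, since the eligibility criteria under Participants set no depression threshold. If both arms worsened instead, false improvement would not arise this way.

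Nor can one say that Bonferroni fails to protect the comparison of arms. Its family is undefined, and spanning the two visits would restore 4-5%.

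A reader might add that seven secondary instruments at 0.05 give 1 − 0.95⁷ = 0.30 for at least one false positive. That needs independence, which is unlikely for mood, stress, anxiety and sleep in the same people. Correcting outcomes already labelled secondary is optional, so this is not part of the error.

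Finally, a condensed article may leave covariates and the exact primary contrast to a fuller plan. That is fair for baseline adjustment taken alone. It does not cover the within-group tests, which the article itself states as inferential; a later plan would have to reverse that statement, not just add detail.

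**Conclusion.** The point holds in a limited form. The Statistical Analysis section lists within-arm pre-post changes among its tests at 0.05 and designates no test or visit for the BDI. The fault is that lack of designation, not an invalid model.

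The consequence ranges from small to serious. The misleading one-arm pattern has a chance of about 1% with no shared trend and about 15-25% with an assumed shared improvement of 0.3-0.5 SD at r = 0.5-0.7. Choosing between two unadjusted visits gives 8-9% error.

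The gain in power from baseline adjustment (0.92 against 0.84 unadjusted and 0.76-0.88 for the interaction) rests on an assumed 0.8 SD effect and r = 0.5. Baseline adjustment is the more efficient choice, not the only valid one.

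**What to change.** In the Statistical Analysis section:

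- State that the single primary test is the between-arm difference in BDI at 4 weeks, adjusted for baseline BDI, two-sided at 0.05.
- Make the 15-day difference secondary.
- Report within-arm changes as means with confidence intervals, without p-values, and state that no efficacy claim will rest on them.
- Optionally, label the secondary instruments as exploratory.

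This changes wording only and needs no extra participants, visits or data. The price is that within-arm p-values can no longer support a claim.
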